## Abstract

**Background:**

Colon cancer is one of the most common cancers in Finland and worldwide. Cancer-related malnutrition is a well-known risk factor for increased morbidity and mortality after surgery, and it is associated with complications and longer hospitalizations. There are no established recommendations on how to improve the nutritional status of colon cancer patients´ during the perioperative phase. Administration of simple oral nutritional supplements has been suggested to reduce complication rates, but evidence to support this practice is scarce.

**Methods:**

The Peri-Nutri trial is a prospective, multicenter, randomized, controlled trial. Its primary endpoint is to evaluate whether perioperative oral nutritional support (ONS) decreases the number of complications during the 30-day follow-up after surgery. Secondary endpoints are to study the effect of ONS on quality of life after surgery, length of stay in institutional care, 90-day mortality rate, five-year disease-free survival and overall survival. The patients with a Nutritional risk screening 2002 (NRS-2002) questionnaire result between 2 and 5 (≥ 3 are classified at risk of malnutrition) will be randomized (1:1 ratio) into either the intervention or control group. The intervention group will receive preoperative ONS two weeks before the operation, and nutritional support will continue 10 days after the operation. The control group will not receive ONS. A total of 318 patients will be randomized into two groups and patients are followed five years.

**Discussion:**

Peri-Nutri study evaluate the impact of ONS to short-term and long-term postoperative morbidity and mortality rates of colon cancer patients undergoing curative surgery. If ONS will decrease patients´ morbidity and mortality, that has a huge impact on patients´ quality of life and also to financial cost.

**Trial registration:**

ClinicalTrials.gov, NCT03863236, Registered 25 February 2019.

**Supplementary Information:**

The online version contains supplementary material available at 10.1186/s40795-022-00591-y.

## Background

Colon cancer is one of the most common cancers both in Finland and worldwide. There were a total of 2331 new colon cancer patients in Finland in 2019. The incidence of colon cancer is 42.22/100,000 [1]. The curative treatment of colon carcinoma includes a surgical resection of the tumor and postoperative adjuvant chemotherapy when indicated. The majority of operations are completed by using laparoscopic techniques.

The prevalence of malnutrition varies between 15 and 85% of patients with cancer [2–4]. It is a well-known risk factor for increased morbidity and mortality in surgery, and it is associated with longer hospital stays and a diminished quality of life [3, 5–7]. Preoperative malnutrition in gastrointestinal cancer patients is shown to be an independent risk factor for complications after surgery [3, 6–9]. It has been shown that 39–60% of newly diagnosed colon cancer patients are at risk for malnutrition and that 4% of patients are malnourished [8, 10]. These patients were more vulnerable to complications than patients without risk (62% vs 39.8%, *p* = 0.004), and they also had a higher mortality rate (8% vs 1.6%, *p* = 0.033) [8].

Although malnutrition is common among gastrointestinal cancer patients, there are only a few randomized controlled [10–15] and prospective cohort [16–18] studies concerning perioperative nutrition and treatment outcomes. Preoperative oral nutritional support (ONS) has been suggested to decrease complication rates [13, 14, 16–19], but some studies did not find this treatment beneficial [10–12, 15].

The results of previous randomized controlled studies have varied. In a study by Kabata et al., the patients had various cancers. They reported favorable effects with preoperative ONS for gastrointestinal cancer patients with no signs of malnutrition. A 14-day-long preoperative period with an oral nutritional supplement significantly decreased severe complications [14]. Whey protein was used as an ONS prior to colorectal cancer surgery with promising results in terms of improvements in a six-minute walk test in patients prior to surgery. However, due to the small sample size, the results were not statistically significant and ONS did not improve postoperative outcomes [10]. Concordantly, two studies found no significant differences in major complications or well-being in patients after major gastrointestinal surgery [13] or after colorectal surgery [11]. In two studies, groups consisted of surgical patients with both benign and malignant diseases [12, 13]; in one study, they consisted of hepatocellular cancer patients [15]. In two studies, the nutritional state was not considered in randomization, causing possible bias to the study groups [11, 12].

There have been a few cohort studies on perioperative nutrition. In a prospective 1,085 patient cohort study with benign and malignant abdominal surgical patients, malnourished patients (NRS score at least 5) receiving either parenteral or enteral nutrition prior to gastrointestinal surgery had a lower rate of infectious complications than the controls [16]. In another prospective cohort study, hospitalized patients, including abdominal surgical patients at risk of malnutrition, benefitted from enteral nutritional support because they had fewer complications than controls, whereas the patients with a normal nutritional status did not show improvement with nutritional support [17]. In a study by Wu et al., perioperative nutritional support was revealed to be crucial in moderately and severely malnourished gastrointestinal cancer patients. Most patients (68%) received parenteral nutrition [18]. In a retrospective study of ‘non-risk’ colorectal cancer patients, who did not receive postoperative nutritional support had a higher rate of postoperative complications and a longer postoperative hospital stay [19].

A review article previously evaluated nutrition-only prehabilitation and multimodal prehabilitation (ONS with exercise) on outcomes of colorectal cancer patients undergoing surgery. They found that any prehabilitation shortened the length of hospital stay after surgery and may be a protective factor for postoperative complications [20]. A randomized controlled trial revealed that a trimodal program four weeks before surgery in colorectal cancer patients significantly increased patients’ walking capacity [10]. Nutritional counseling has also been shown to be effective in colorectal cancer patients’ nutritional intake, quality of life (QoL) and status [21, 22]. In our study, all patients are given written information about recommended nutrition for colon cancer patients before and after surgery.

There are no randomized controlled studies addressing how to improve the nutritional status of colon cancer patients with a low to moderate risk of malnutrition in the perioperative phase and whether it is possible to reduce the number of complications by administering a simple oral supplement during the perioperative period. Previous randomized controlled studies have included both colon and rectal cancer patients [10, 11, 19, 21, 22]. Rectal cancer treatment differs from colon cancer treatment. It may include neoadjuvant radiotherapy or chemoradiotherapy, which may confound the results. The sample sizes of previous studies were small and nutritional status was not taken into account during the randomization, so the study groups may have differed at baseline.

If perioperative ONS decreases morbidity and mortality after colon carcinoma surgery, it could have a significant impact on decreasing human suffering. This would also decrease financial costs by decreasing complications and hospital stays.

## Objectives

### Primary objective

The primary aim of this study is to evaluate whether perioperative ONS used two weeks prior to surgery and 10 days after surgery can decrease 30-day period postsurgical complication rates.

### Secondary objectives

Secondary aims are to investigate whether ONS improves the nutritional status of colon cancer patients, reduces 30- and 90-day mortality, shortens the stay in institutional care and improves patients’ quality of life as well as their five-year disease-free and overall survival rates and improves tolerance to adjuvant chemotherapy with fewer side effects.

## Methods

### Study setting

This study is accomplished at the Oulu University Hospital, the Kuopio University Hospital, the Seinäjoki Central Hospital and the Rovaniemi Central Hospital in Finland.

### Trial design

The Peri-Nutri trial is a prospective, multicenter, nonblinded, randomized study. Consecutive patients diagnosed with primary colon adenocarcinoma and considered for radical surgical procedures are enrolled in this study. The trial was approved by the Ethics Committee at Oulu University Hospital and registered at Clinical Trials NCT03863236. Patient recruitment started in April 2019 at the Oulu University Hospital, November 2019 at the Seinäjoki Central Hospital and in April 2021 at the Kuopio University Hospital. Recruitment will be completed on approximately April 1, 2023. The study flow is illustrated in Fig. 1. The design of this study is open label. Blinding is not possible because there is no adequate ONS-placebo product to use. Blinding is not possible for surgeons because they recruit the patients, participate in patient care and collect the data.

**Fig. 1 Fig1:**
[figure not shown]
Flowchart

### Eligibility criteria

Consecutive patients examined for colon cancer at each research site will be evaluated for their suitability for inclusion in the trial. After all inclusion and exclusion criteria are verified, the patient will be informed about the study at the outpatient clinic and informed consent will be obtained.

#### Inclusion criteria

18 years or olderPrimary colon adenocarcinomaCurative operation is possiblePatient has a life expectancy of at least 12 monthsPatient signs the informed consent and agrees to attend all study visits

#### Exclusion criteria

Recurrent colon adenocarcinomaMetastatic diseaseCancer that will require multiorgan resectionPregnant or suspected pregnancyPatients with a comorbid illness or condition that would preclude the use of surgery (ASA 5)Patients with concurrent or previous malignant tumors within five years before study enrollmentPatient undergoing emergency proceduresDialysisLiver dysfunction; Child–Pugh B or worseNRS score < 2 or > 5Body mass index (BMI) under 18.5Weight loss of 15% or more in the past six monthsSerum albumin less than 30 without liver or renal dysfunctionChronic malnutrition: short bowel syndrome, previous gastrectomy, pancreatic dysfunctionLanguage barrier, impaired cognition or other reasons why informed consent is not possibleAllergy to ONS contentsPatient not willing to participate

### Outcomes

#### Primary outcome

The primary outcome is the number of complications during the 30-day period postoperatively.

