### Sample size

The 30-day complication rates in previous studies [10, 12–17, 23] varied from 8.2 to 77.3% (8.2 to 46.9% for patients receiving ONS, and 12.0 to 77.3% for patients without ONS). Since the sample size of those studies varied from 43 to 432 participants, we calculated weighted 30-day complication rates by using the size of the study as a weight. Accordingly, the weighted 30-day complication rate is 22.0% for patients receiving ONS and 14.9%-unit higher (i.e., 36.9%) for patients without ONS. Further, assuming a two-sided 5% significance level (alfa) and a power of 80% (1-beta) we would need 143 patients per group to show ONS being superior. Accounting for a 10% drop-out rate, the final sample size needed is 159 per group. To recruit this number of patients a 48-month inclusion period was anticipated.

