### Statistical analysis

This is a superiority trial. Participants will remain in the groups to which they were originally assigned (intention to treat principal). Additionally, per protocol analyses will be performed as sensitivity analyses. In the per protocol analyses, protocol violation is deemed if a patient consumed < 50% of nutritional drinks in the intervention group or in control group if a patient drank more than 5 nutritional drinks.

All analyses will be adjusted by stratification variable (Nutritional status (NRS 2002) 2, 3–4 or 5). Additionally, the crude outcomes will be reported. The treatment effect will be assessed by odds ratios for categorical data, hazard ratios for survival data and mean differences for continuous data. Random effect models will be used in the case of repeatedly measured data (> 2 repeated measurements). If the incidence of outcome of interest is common (> 10%) then odds ratios will be converted to risk ratios [39].

The treatment effect will be calculated separately for each NRS 2002 stratification class (2, 3–4 and 5). However, as the sample size calculation was performed only for the total treatment effect, the results of the stratified analyses are hypothesis generating only.

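### The primary outcome is worded as a count of complications, but the sample size and its 80% power are derived for the proportion of patients with a complication, and no effect measure is assigned to it

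*Protocol article*

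**What the plan says.** Three parts of the protocol article describe the primary outcome, in different terms.

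- **Count.** The Primary outcome section reads: "The primary outcome is the number of complications during the 30-day period postoperatively". The abstract's Methods agree, asking whether ONS "decreases the number of complications during the 30-day follow-up after surgery". The Data collection section records complications after the primary operation and after any reoperation, and grades each one by Clavien-Dindo, so one patient can have several.
- **Rate.** The Primary objective asks whether ONS "can decrease 30-day period postsurgical complication rates".
- **Percentage.** The Sample size section states that "the weighted 30-day complication rate is 22.0% for patients receiving ONS and 14.9%-unit higher (i.e., 36.9%) for patients without ONS", "assuming a two-sided 5% significance level (alfa) and a power of 80% (1-beta"), and arrives at 143 per group, or 159 after a 10% drop-out allowance.

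The Statistical analysis section gives a general rule: "The treatment effect will be assessed by odds ratios for categorical data, hazard ratios for survival data and mean differences for continuous data". Analyses are adjusted for NRS-2002 stratum, and odds ratios are converted to risk ratios where the outcome is commoner than 10%. The section does not say which of these measures applies to the primary outcome, and it lists none specific to counts.

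**The concern.** A count per patient and a yes/no outcome per patient are different endpoints. They have different effect measures, different variances and different power. If the defined endpoint is the count, the trial was sized for something else and the 80% cannot be claimed for it. If the proportion is meant, the definition that readers and the registry will hold the trial to is wrong.

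The analysis section does not settle the matter. A count handled as continuous data would get a mean difference; an outcome handled as categorical would get an odds ratio, then a risk ratio. Both fit the text. The confirmatory comparison is therefore not identified in this document, and the two candidates need not agree on statistical significance.

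**Working it through.** **Inputs from the document.** Rates p1 = 0.369 (no ONS) and p2 = 0.220 (ONS); two-sided 5% level; 80% power; 1:1 allocation; 143 per group before and 159 after drop-out.

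**Step 1. Reproduce the stated figure.** For two independent proportions with unpooled variance:

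n = (1.960 + 0.842)² × [p1(1 − p1) + p2(1 − p2)] / (p1 − p2)²
= 7.849 × (0.2328 + 0.1716) / 0.149²
= 7.849 × 0.4044 / 0.02220 = 142.98, so 143 per group.

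Drop-out: 143 / 0.90 = 158.9, so 159. Both figures reproduce. Power at 143 per group is 80.0% with unpooled variance and 79.2% with pooled variance. The arithmetic is right, and it is arithmetic for a binary outcome.

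**Step 2. Ask what 143 per group gives for a count.** This needs a mean count and a dispersion, which the document does not give. Everything below is therefore assumed, and three structures are shown to span a range.

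*(a) The rates are proportions with any complication, and affected patients have the same average number of complications, m, in both groups.* With a shifted Poisson count (one plus a Poisson with mean m − 1), the per-group variance is p(m² + m − 1) − (pm)² and the difference in means is (p1 − p2)m. For m = 2 the variances sum to 1.3004 + 0.9064 = 2.2068 and the difference is 0.298. Then z = 0.298 / √(2.2068/143) = 2.40, and power = Φ(2.40 − 1.96) = 67%.

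| m (assumed) | Power, mean difference | n per group for 80% |
|---|---|---|
| 1 (binary) | 80% | 143 |
| 1.25 | 71% | 177 |
| 1.5 | 68% | 190 |
| 2 | 67% | 196 |
| 2.5 | 67% | 193 |

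*(b) Counts are Poisson or negative binomial (shape k), with means chosen so that the chance of at least one complication is 36.9% and 22.0%.* The mean is −ln(1 − p) for Poisson and k[(1 − p)^(−1/k) − 1] otherwise. The log rate ratio has variance (1/μ1 + 1/μ2 + 2/k)/143. For k = 1 the means are 0.585 and 0.282, the variance is 0.0507, z = 3.24, and power = Φ(3.24 − 1.96) = 90%.

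| k (assumed) | Means | Power, rate ratio | Power, mean difference | Power, Wilcoxon (4,000 simulated trials) |
|---|---|---|---|---|
| Poisson | 0.460, 0.248 | 84% | 85% | 83% |
| 1 | 0.585, 0.282 | 90% | 89% | 86% |
| 0.5 | 0.756, 0.322 | 94% | 91.5% | 87% |
| 0.25 | 1.327, 0.425 | 98% | 94% | 90% |

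The rate-ratio test would need 128, 108, 91 and 68 per group for 80% power.

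*(c) 0.369 and 0.220 are themselves mean complications per patient.* The log rate ratio is ln(0.220/0.369) = −0.517. For Poisson, the variance is (2.710 + 4.545)/143 = 0.0507, z = 2.30, and power = 63%. For k = 1, 0.5 and 0.25, power is 53%, 45% and 35%. For 80% power, the numbers needed are 213, 272, 331 and 448 per group.

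**Step 3. Compare.** Across these assumptions, power for a count at 143 per group runs from about 35% to 98%. None of the count calculations returns 143; structure (a) does so only at m = 1, where the count has become a yes/no outcome.

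**The case against.** The strongest reply is that the wording is loose but the intent is clear. The objective speaks of rates, the planning figures are percentages that reproduce as proportions, and the conversion of odds ratios to risk ratios makes sense only for a binary outcome. On that view, the number of complications simply means how many patients have one. Model detail also commonly sits in an analysis plan, which is not shown here.

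Much of this stands. The proportion is probably what was intended, and the absence of a named count model is not a defect in itself. But the count appears in both places that define the endpoint. An analysis plan can name a test; it cannot make a published endpoint match a sample size built on a different one.

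Three stronger readings are tempting and are not supported:

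- **That a count analysis would be underpowered.** Structure (a) points that way, but it assumes that ONS leaves the number of complications per affected patient unchanged. Structure (b), with the same any-complication rates, gives more than 80%. For the same reason, no figure for how often the two analyses would disagree on significance can be taken from the document.
- **That the primary analysis will be chosen after results are seen.** This article leaves the choice open; it does not show that the choice stays open in an analysis plan.
- **That unblinded surgeons recording events, without a severity threshold, is part of this defect.** The article discloses the open-label design and says why: "Blinding is not possible for surgeons because they recruit the patients, participate in patient care and collect the data". That is a separate matter and does not bear on count versus proportion.

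**Conclusion.** The inconsistency is real and visible in the document itself. The primary outcome is worded as a count, the trial is sized on a proportion, and no effect measure is assigned to the primary outcome. The 143 and 159 per group are correct for the proportion (142.98, rounded up), and the 80% power applies there. For a count, the 80% is unsupported: it could be as low as about 35% or as high as about 98%, depending wholly on assumed means and dispersions. The finding is that the stated power and the stated endpoint belong to different quantities, not that the trial is too small. It does not depend on any of the assumed count distributions, which serve only to show how wide the gap is.

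**What to change.** 1. In the abstract and the Primary outcome section, define the primary outcome as the proportion of patients with at least one complication within 30 days of surgery, recorded yes or no for each patient. Use the same definition of a complication as underlies the rates in the Sample size section, and state it. The article does not show which grades or types those source studies counted, so no grade range should be presumed to be the one the sample size used.
2. In the Statistical analysis section, name the odds ratio adjusted for NRS-2002 stratum, converted to a risk ratio, as the single primary analysis. Both planning rates exceed 10%, so the existing conversion rule would apply if they hold.
3. List the number of complications per patient and the comprehensive complication index as secondary outcomes.

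The cost is a short amendment, notified to the ethics committee, and a matching registry update, best made before database lock. The data needed are already collected, no patients are added, and the sample size stays at 159 per group.

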#### Secondary outcomes

Secondary outcomes are quality of life after surgery, length of stay in institutional care, 90-day mortality, tolerance to adjuvant chemotherapy and five-year disease-free and overall survival.

### Sample size

The 30-day complication rates in previous studies [10, 12–17, 23] varied from 8.2 to 77.3% (8.2 to 46.9% for patients receiving ONS, and 12.0 to 77.3% for patients without ONS). Since the sample size of those studies varied from 43 to 432 participants, we calculated weighted 30-day complication rates by using the size of the study as a weight. Accordingly, the weighted 30-day complication rate is 22.0% for patients receiving ONS and 14.9%-unit higher (i.e., 36.9%) for patients without ONS. Further, assuming a two-sided 5% significance level (alfa) and a power of 80% (1-beta) we would need 143 patients per group to show ONS being superior. Accounting for a 10% drop-out rate, the final sample size needed is 159 per group. To recruit this number of patients a 48-month inclusion period was anticipated.

### Randomization and allocation

Patients undergoing surgery for primary adenocarcinoma of the colon and fulfilling the inclusion criteria will be randomized on their preoperative visit to the outpatient clinic approximately two to three weeks prior to surgery after signing an informed consent form. The patients will be randomly allocated (1:1 ratio) to either an intervention group or a control group according to a computer-generated list compiled by a biostatistician otherwise uninvolved in the clinical care of the trial patients. Allocation will be stratified according to NRS-2002 results (2, 3–4 and 5) and blocked within strata using random permuted blocks (block sizes 2, 4, 6 and 8). A separate randomization list will be created for each participating center. All patients undergoing surgery for colon cancer will be approached and assessed for eligibility and, once their consent is obtained, randomization will be performed. The random allocation will be performed in Case Report Forms (eCRF) where the treatment group cannot be seen before both patient consent and all eligibility criteria fulfilled.

